**Research project: Influence of a protein diet on the colonic metabolism and phosphor metabolism in healthy volunteers**

# Introduction

Recently, there is an increased interest in the use of high-protein/low-carbohydrate diets (protein diets) in the area of weight loss and treatment of disease. Protein intake results in increased satiety compared to other nutrients. Protein diets result in increased loss of fat in comparison with diets high in carbohydrates or low in proteins. Protein diets were also shown to reduce the risk on cardiovascular diseases. Positive effects were also found on body composition, lipid composition in the blood, glucose homeostasis or vitamin status in the body.

An increased protein intake probably results in an increased amount of protein in the colon. Components from endogenous or exogenous origin entering the colonic lumen will undergo bacterial metabolisation or fermentation. The resulting metabolites play an important role in energy metabolism, physiology and pathophysiology of the colon. The quality and quantity of the bacterial metabolites depends on the characteristics of the bacterial flora, the transit time through the colon and substrate availability. Carbohydrates are fermented to short chain fatty acids (SCFA: acetate, propionate, butyrate), which are generally considered to be beneficial for the colonocytes of the host. Fermentation of proteins also results in the production of SCFA, but also of potentially toxic metabolites such as amines, ammonia, mercaptanes and phenol derivatives. Ammonia and phenol derivatives are often used as cancer risk markers. Until now, the effects of a protein diet on the colon has not been investigated, therefore the goal of this present is to investigate the influence of a high dose of proteins on colon metabolism.

In both patients with chronic kidney disease and the general population serological phosphor concentration is a predictor of cardiovascular morbidity and mortality. Serological phosphor also has an important influence on the bone metabolism, also in patients with a normal kidney function. Serological phosphor concentration reflects the balance between gastro intestinal absorption, transport from and to the bone and urinary excretion. Average daily phosphor intake is 1600 mg. Dietary proteins are an important source of exogenous phosphor. Bio availability and the contribution of additives (up to 1000 mg/d) have to be considered. Parathyroid hormone (PTH) and FGF-23 induce urinary phosphor loss and, therefore, play an important role in renal phosphor homeostasis. Serum levels of PTH, but not FGF-23, increase quickly after a single oral phosphor bolus. Data concerning the physiological response to a longer term high protein diet (phosphor) are scarce.

In the proposed study protocol the influence of a high versus a low protein diet on the colonic metabolism will be investigated. As secondary end point the influence of a high versus a low protein diet on phosphor homeostasis will be studied. In Belgium, average daily protein intake is 16% of total dietary intake (<http://www.iph.fgov.be/epidemio/epinl/index5.htm>), which is higher than the recommendations by High Health counsel for Belgium. These recommendations state that the average protein need is 9-11% of total energy intake ([https://portal.health.fgov.be/pls/portal/docs/PAGE/INTERNET_PG/HOMEPAGE_MENU/ABOUTUS1_MENU/INSTITUTIONSAPPARANTEES1_MENU/HOGEGEZONDHEIDSRAAD1_MENU/BROCHURES1_DOCS/HGR%207145-2%20070118_NL.PDF](https://portal.health.fgov.be/pls/portal/docs/PAGE/INTERNET_PG/HOMEPAGE_MENU/ABOUTUS1_MENU/INSTITUTIONSAPPARANTEES1_MENU/HOGEGEZONDHEIDSRAAD1_MENU/BROCHURES1_DOCS/HGR 7145-2 070118_NL.PDF)). Energy intake will be the same during this study, while protein intake during 2 intervention periods will be increased to 30% of total daily energy intake (high protein diet) or decreased to 9% of total daily energy intake (low protein diet).

# GOALS

In the proposed project the influence of an isocaloric diet with high/low protein intake versus a normal diet on the colonic metabolism in healthy volunteers will be investigated. To this purpose parameters of colonic metabolism will be investigated:

- Analysis of ammonia metabolism in the colon after administration of lactose-[15N, 15N]-ureid
- Analysis of urinary p-cresol excretion as a marker of protein fermentation
- Analysis volatile organic compounds (VOC) in feces
- Analysis of genotoxicity of fecal water using the Comet Assay
- Analysis of cytotoxicity of fecal water using the WST-1 assay

Secondly, the influence of an isocaloric diet with high/low protein intake versus a normal diet on the phosphor homeostasis in healthy volunteers will be evaluated. To this purpose the following parameters are investigated:

- Analysis of biochemical parameters of phosphor homeostasis (serum calcium and phosphor, calcidiol, calcitriol, PTH, FGF-23)
- Analysis of parameters of bone formation and bone resorption
- Analysis of dietary phosphor and calcium
- Analysis of urinary excretion of calcium and phosphor

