## Subjects

Twenty healthy subjects will be included in a randomized cross-over study with 10 subjects in each group. Group 1 will start with the high protein diet and switch to the low protein diet. In group 2 the interventions occur in reversed order (Figure 1). After an explanation of the study and its purpose written consent will be asked (‘Informed consent’: appendix 1).

Inclusion criteria:

- Healthy subjects
- Regular dietary pattern (3 meals per day)
- Age: 18-45 years
- BMI: 18.5-27 kg/m2

Exclusioncriteria:

- Intake of antibiotics one month prior to the study
- Abdominal surgery in the past (except appendectomy)
- Intake of medication influencing the gastrointestinal system 14 days prior to the study
- Consulting a dietician
- Severe liver- or kidney failure
- Vegetarian
- Intake of pre-/probiotics
- Participation to a study using radio-activity 1 year prior to the study

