## ENDPOINTS

The primary endpoints of this study are the effects of a high, low and normal protein diet on the colonic metabolism in healthy subjects. Following parameters will be evaluated (description of used techniques, see above):

- Analysis of fat mass
- Analysis of ammonia metabolism in the colon after administration of lactose-[15N, 15N]-ureid
- Analysis of urinary p-cresol excretion as a marker of protein fermentation
- Analysis volatile organic compounds (VOC) in feces
- Analysis of genotoxicity of fecal water using the Comet Assay
- Analysis of cytotoxicity of fecal water using the WST-1 assay

The secondary endpoints of this study are the effects a high, low and normal protein diet on the phosphor homeostasis in healthy subjects. The following parameters will be evaluated (description of used techniques, see above):

- Analysis of biochemical parameters of phosphor homeostasis (serum calcium and phosphor, calcidiol, calcitriol, PTH, FGF-23)
- Analysis of parameters of bone formation and bone resorption
- Analysis of dietary phosphor and calcium
- Analysis of urinary excretion of calcium and phosphor

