## METHODS

- On day 1 of the study subjects undergo indirect calorimetry used to measure baseline energy need. The result of this measurement and information on physical activity of the subject will be used to calculate the total energy need. These measurements will be performed by Prof. [name].
- During the first week of the study, subjects can follow their normal diet, but are asked to fill in a 7-day dietary journal.
- On day 5 of the 1st week the percentage body fat is measured (impedance measurement) and a test evaluating the colonic metabolism has to be performed.
- Starting the 2nd week of the study the volunteers of group 1 receive a high protein diet during week 2 and 3 of the study, while the volunteers of group 2 receive a low protein diet during week 2 and 3 of the study.
- Three days before the end of the first intervention period (=day 19) the subjects again perform a test (impedance measurement + colonic metabolism), after which they switch diet for the next 2 weeks.
- Three days before the end of the second intervention period (=day 33) the last test is performed.
- During week 3 and week 5 the volunteers again fill in a 7-day dietary record.

Subjects maintain their normal physical activity level during the entire period of the study.

On the morning of the test subjects come sober to the laboratory Digestion & Absorption. After donating a baseline urine and blood sample and measurement of the body fat percentage, a test meal is consumed by subjects. Following this test meals urinary and fecal samples have to be collected.

- Test meal:
  - Pancake supplemented with lactose-[15N, 15N]-ureid (75 mg), a capsule containing [3H]-PEG (185 kBq) and a glass water.
- Samples:
  - Urine samples (complete collection): 48h
  - Fecal samples (complete collection): 72h

|  | Day 0 | | Day 5 | | Day 19 | | | | | | Day 33 | | |
| --- | --- | --- | --- | --- | --- | --- | --- | --- | --- | --- | --- | --- | --- |
|  | IC | | Test 1 | | Test 2 | | | | | | Test 3 | | |
|  | |  |  |  |  | |  | |  | |  | | |
| Group 1 (n=10) | | Normal diet | | High protein diet | | | | | Low protein diet | | | |  |
|  | |  | |  |  | |  |  | |  |  | | |
| Group 2 (n=10) | | Normal diet | | Low protein diet | | | | | High protein diet | | | |  |
|  | |  | |  | |  | | |  | | |  |  |
|  | | Dietary journal | |  | | Dietary journal | | |  | | | Dietary journal |  |

IC = indirect calorimetry

Test 1-3: impedance measurement + evaluation of colonic metabolism

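### The diet comparison is stated three ways, and the one in the GOALS, against the normal diet, is not randomised and cannot be separated from a free period effect

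*Protocol*

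**What the plan says.** Three sections describe the diet comparison, each differently.

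- **Introduction:** "the influence of a high versus a low protein diet on the colonic metabolism will be investigated". The same contrast is given for phosphor homeostasis.
- **GOALS:** "influence of an isocaloric diet with high/low protein intake versus a normal diet on the colonic metabolism in healthy volunteers will be investigated". Phosphor homeostasis gets the same comparator. High versus low is not named in this section.
- **ENDPOINTS:** the primary endpoints are the "effects of a high, low and normal protein diet on the colonic metabolism in healthy subjects". No contrast is singled out, and the secondary endpoints follow the same pattern.

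On design, Subjects states: "Twenty healthy subjects will be included in a randomized cross-over study with 10 subjects in each group". What differs between the groups is the order of the high and low protein diets. The schedule under METHODS says "During the first week of the study, subjects can follow their normal diet", and its table puts the normal diet first in both groups. Test 1 is on day 5, Test 2 on day 19 and Test 3 on day 33.

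On energy, the Introduction says "Energy intake will be the same during this study". The Indirect calorimetry section uses the calculated energy need to make the high and low protein diets isocaloric. DESIGN OF ADAPTED DIETS provides menu lists only for the 9% and 30% protein diets. In week 1 intake is recorded in a journal, and nothing sets it.

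**The concern.** The comparison named in the GOALS is the one that randomisation does not protect. Every subject takes the normal diet first and at no other time. Any change between the first test and the later ones therefore appears as an effect of both protein diets against normal. Practice with complete 48 h urine and 72 h faecal collections is one plausible source. The move from self-chosen to prescribed intake is another, and it happens at the same moment.

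Which question the trial asks belongs in the protocol. A SAP can choose a model, but it cannot settle the objective when the protocol gives three answers. If the GOALS were followed as worded, a before/after change could be reported as the result of a randomised cross-over.

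**Working it through.** The protocol gives no alpha, power, effect size or SD, so there is no figure of its own to reproduce. The check is which contrasts the design can estimate, followed by an illustration of size.

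**Inputs.** 20 subjects, 10 per sequence (Subjects). Sequences normal-high-low (N-H-L) and normal-low-high (N-L-H), with tests on days 5, 19 and 33 (METHODS, schedule).

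**1. Estimability.** The model has 20 subject effects, 2 period columns (Tests 2 and 3 against Test 1) and 2 diet columns (high and low against normal).
- Rows: 20 × 3 = 60. Columns: 20 + 2 + 2 = 24. Rank: 23.
- The one dependency is high + low = period 2 + period 3, which is true in every row. Both sides are 0 at Test 1 and 1 at Tests 2 and 3.
- A contrast is estimable if adding it as a row leaves the rank unchanged. High − normal: no. Low − normal: no. High − low: yes.
- For comparison, if the normal diet could fall in any position (six sequences, 3 subjects each), the matrix is 54 × 22 with rank 22 and all three contrasts are estimable. The fixed first position causes the aliasing.

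**2. What a period effect does.** Let p2 and p3 be the shifts at Tests 2 and 3 relative to Test 1, the same in both groups.
- High − normal: group 1 gives the true difference + p2, and group 2 gives it + p3. With equal groups the bias is (p2 + p3)/2. Low − normal has the same bias.
- High − low: group 1 gives the true difference + p2 − p3, and group 2 gives it + p3 − p2. The average is the true difference, so the bias is 0.

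**3. Illustration of size.** Assume no diet effect and a mean shift of d, in SDs of the within-subject difference. Use a paired t-test with n = 20, two-sided 0.05 and noncentrality d × √20. The values of d are assumptions; the protocol gives none.

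| Assumed shift d | Noncentrality | Chance of a false diet-versus-normal finding |
|---|---|---|
| 0 | 0 | 5.0% |
| 0.25 | 1.12 | 18.6% |
| 0.5 | 2.24 | 56.5% |
| 0.75 | 3.35 | 88.9% |

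**4. A linear trend in place of free periods.** The tests are equally spaced (19 − 5 = 14 days; 33 − 19 = 14 days). Code time as 0, 1, 2 and suppose a + b·time + c·high + d·low = 0 in every cell. Test 1 gives a = 0. High at Tests 2 and 3 gives b + c = 0 and 2b + c = 0, so b = c = 0. Low then gives d = 0. The columns are independent, so all three contrasts become estimable. The slope comes from Test 3 against Test 2. It is then extrapolated back from the mean of those tests to Test 1, a distance of (19 + 33)/2 − 5 = 21 days, or 1.5 intervals. A step that occurs only after the first test is not captured.

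**5. Energy.** The two protein diets share one target, calculated need. Week 1 has a record but no target. The Introduction's statement covers the whole study; the means of achieving it cover only the two intervention diets.

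**The case against.** A week on habitual diet before a randomised two-period crossover is an ordinary design. The randomised contrast is intact, and the choice of model may sit in a SAP that is not shown. All of this stands, and it limits the weight of the point. It does not remove the conflict between the Introduction, GOALS and ENDPOINTS over the question asked.

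Some of the possible drift is also addressed. The protocol corrects 15N excretion for transit time with labelled PEG and asks subjects to keep their usual activity. These measures help, but they do not cover collection practice or the change to prescribed food.

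A reader might infer three stronger things that the documents do not support.

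- **That the normal week is not isocaloric with the protein diets.** Nothing shows that week-1 intake will differ from calculated need. The menus are said to be adapted to each subject's energy intake, and the journals in weeks 1, 3 and 5 allow a comparison afterwards. In the GOALS, isocaloric may also describe only the high and low diets. What can be said is that energy matching with week 1 is asserted and not controlled.
- **That the comparison with normal is the trial's declared main one.** The GOALS name only that comparison, but they call no diet contrast primary, and the other two sections differ from them.
- **That no analysis could deal with a time trend.** A linear trend could be modelled, as shown above, at the price of extrapolation. A shift confined to the first test could not.

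**Conclusion.** The point holds as one of inconsistent objectives and an unprotected comparator, and it should be fixed. The diet contrast differs across the three sections. The contrasts with the normal diet are completely aliased with an unrestricted period effect, and reading them as diet effects rests on assuming no first-test shift (or, with a linear term, a straight trend through all three tests). If period is ignored the bias is (p2 + p3)/2. Its actual size is unknown, because the protocol contains no estimate of drift, and the false-positive rates above are illustrations only.

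High versus low is estimable and is not biased by a period effect common to both groups when period is in the model. Nothing here counts against that comparison.

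**What to change.** Make the Introduction, GOALS and ENDPOINTS agree:

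1. Name high versus low protein as the primary contrast: Test 2 against Test 3, within subject, allowing for period. Use the same contrast for the phosphor endpoints.
2. Describe Test 1 on the normal diet as the baseline, and comparisons with it as non-randomised, exploratory changes from baseline.
3. Limit the isocaloric and equal-energy statements to high versus low. For week 1, say that intake is recorded and not set.

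This needs no extra subjects, visits or assays. The real cost is scientific: the question that the GOALS now ask, protein diet against normal diet, becomes exploratory.

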# METHODS

## Indirect calorimetry

Baseline energy use is measured using indirect calorimetry. Calorimetry will be performed under standard conditions (thermoneutral environment, sober and at rest). Using a ventilated-hood system the amount of O2 and CO2 in inhaled and exhaled air is measured each minute. In total there will be measured for 25 minutes. In combination with an estimation of physical activity, determined using the validated Baecke questionnaire, total energy need will be calculated. This result will be used to design isocaloric high and low protein diets.

## Body composition

Measurement of the body composition (fat mass and fat free mass) will be done using the bio-electrical tetrapolar impedance method (Bodystat 1500). A small current (800 µA, 50 kHz) is used to measure the resistance of the body. Using population specific regression equations fat mass and fat free mass are calculated. This measurement is non invasive, takes only a few minutes, is very reproducible and validated (to the deuterium dilution method).

## Analysis of the colonic ammonia metabolism after administration of lactose-[15N, 15N]-ureid

Using lactose-[15N, 15N]-ureid a known amount of [15N] is transported to the colon. Lactose-[15N, 15N]-ureid is not metabolized in the small bowel and reaches the colon, unchanged. In the colon the bound between lactose and [15N, 15N]-urea is specifically hydrolyzed by bacterial enzymes. The resulting [15N, 15N]-urea will mix with the natural present urea and will become available for the microbiota in the colon. [15N, 15N]-urea will be further hydrolyzed to [15N]-NH3, which can be absorbed by the bacteria and excreted in feces. [15N]-NH3 can also be absorbed by the colonocytes and, after metabolisation in the liver, urinary excreted as [15N]-urea. By determining how much 15N appears in urine and feces, the metabolism of nitrogen containing compounds can be studied. Tritium-labeled polyethyleenglycol (PEG) is administrated together with the 15N-biomarker to correct 15N-excretion for changes in transit time. [3H]-PEG will not be absorbed or metabolized in the gastrointestinal system and leaves the body unchanged in the feces. The recovered amount of [3H]-PEG can be quantified using liquid scintillation.

## Analysis of urinary p-cresol excretion as a marker of protein fermentation

Proteins escaping digestion in the small bowel and endogenous proteins and peptides produced by the microbiota are fermented in the colon to a variety of metabolites, such as p-cresol. p-Cresol is a unique bacterial metabolite (it is not produced by human enzymes) of tyrosine. p-Cresol is absorbed by the colonic mucosa, conjugated with sulphate or glucuronide and urinary excreted. Therefore, urinary p-cresol excretion is a measure for the amount of protein degradation in the colon. After extraction from the matrix, p-cresol will be measured using GC-MS.

## Analysis of VOC profiles in feces

The analysis of VOC profiles in fecal samples will give additional information on the metabolic activity of microbiota. Special attention will be given to SCFA (acetate, propionate, butyrate, …) branched chain fatty acids (Isobutyrate, isovalerate, …), sulphur containing compounds (dimethyl sulphide, trimethyl sulphide, …) and phenolic compounds (indol, skatol, phenol, p-cresol).

## Analysis of fecal water genotoxicity using the Comet Assay

The Comet Assay (or Single Cell Gel Electrophoresis Assay) is a technique that allows to detect and quantify single and double strand DNA-breaks on cellular level. To determine the DNA damage induced by fecal water (supernatans generated after ultracentrifugation of fecal samples), HT-29 clone 19A cells (a human colon cell line) will be incubated with fecal water. Next the incubated cells are cultured and put on a gel. During electrophoresis the DNA is attracted to the cathode. In case of breaks in the DNA, the DNA will move more easily through the gel. After staining a comet-like structure will appear. The length of the tail indicates the amount of DNA damage (numbers of breaks in the DNA).

# Analysis of fecal water cytotoxicity using the WST-1 assay

The WST-1 cytotoxicity test measures the metabolic capacity of living cells to reduce the yellow tetrazolium compound [4-(3-(4-iodophenyl)-2-(4-nitrophenyl)-2H-5-tetrazolio)-1,3-benzene disulfonate) (WST-1)] to the red formazan. After exposure of colonic cells (HT-29) to fecal water for 72h, the medium is replaced with a WST-1-solution and incubated for 2h and 4h at 37°C. The intensity of the color is measured spectrophotometrically (570 nm) and is proportional to the number of living cells.

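### The WST-1 read-out is fixed at 570 nm, but the yellow-to-red colour change the protocol describes points to a shorter wavelength, so one of six primary parameters is probably read off-peak

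*Protocol*

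**What the plan says.** The protocol's section on the WST-1 assay says that the test measures the capacity of living cells "to reduce the yellow tetrazolium compound" WST-1 "to the red formazan". After 72 h of exposure of HT-29 cells to fecal water, "the medium is replaced with a WST-1-solution and incubated for 2h and 4h at 37°C". The read-out is then fixed: "The intensity of the color is measured spectrophotometrically (570 nm) and is proportional to the number of living cells".

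No other wavelength appears. The section gives no absorption spectrum, peak, reference wavelength, blank correction or assay specification.

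Under ENDPOINTS, the protocol lists "Analysis of cytotoxicity of fecal water using the WST-1 assay" as one of six parameters that make up the primary endpoints. The number of subjects is given under Subjects: "Twenty healthy subjects will be included in a randomized cross-over study with 10 subjects in each group".

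**The concern.** The colour description and the wavelength fit poorly. A solution takes the colour of the light it lets through. A red one passes long wavelengths and absorbs shorter ones, mainly blue-green to green. A dye with its main band centred at 570 nm would look violet. By the protocol's own account of the product, 570 nm therefore probably lies beyond the peak, on the long-wavelength side.

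A laboratory that follows the text literally would set its reader to 570 nm. Off the peak, the same number of living cells gives a smaller absorbance, while reader noise and the absorbance of plate and reagent need not shrink with it. The viability reading becomes less precise, and with 20 subjects added assay noise is unwelcome. A real difference in cytotoxicity between the diets would then be harder to detect.

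**Working it through.** The 570 nm figure is a setting and cannot be re-derived from anything else in the protocol. Two checks are possible: how much signal could remain at 570 nm, and what an off-peak reading does to the comparison.

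**Inputs from the protocol:** read-out 570 nm; substrate yellow; product red; the same evaluation of colonic metabolism at three tests per subject (days 5, 19 and 33).

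**Inputs assumed, because the protocol does not give them:** a single Gaussian absorption band, peak between 440 and 540 nm, width at half height W between 80 and 150 nm.

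**Step 1: signal kept at 570 nm.** Fraction of peak absorbance = exp(−4 ln 2 × ((570 − peak)/W)²). For example, for a 500 nm peak and W = 100 nm: (70/100)² = 0.49; 4 ln 2 × 0.49 = 1.359; exp(−1.359) = 0.257.

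| Assumed peak | W = 80 nm | W = 100 nm | W = 120 nm | W = 150 nm |
|---|---|---|---|---|
| 440 nm | 0.001 | 0.009 | 0.039 | 0.125 |
| 460 nm | 0.005 | 0.035 | 0.097 | 0.225 |
| 480 nm | 0.030 | 0.106 | 0.210 | 0.369 |
| 500 nm | 0.120 | 0.257 | 0.389 | 0.547 |
| 520 nm | 0.339 | 0.500 | 0.618 | 0.735 |
| 540 nm | 0.677 | 0.779 | 0.841 | 0.895 |

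Every cell is below 1, which is the direction of the concern. The range, about 0.1% to 90%, is too wide to state a size.

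**Step 2: effect on the comparison with the blank subtracted.** Let r be the fraction from step 1, and c₁ and c₀ the amounts of product in two samples. Blank-corrected absorbance is proportional to r × c, so the ratio of two samples is (r c₁)/(r c₀) = c₁/c₀. The fraction r cancels. If it is the same at all three tests, the relative difference between diets keeps its expected value and only its precision falls.

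**Step 3: effect if the blank is not subtracted.** Assume 1.5 AU of product absorbance at the peak at full viability, a constant background of 0.05 AU, W = 100 nm and a true fall in viability of 20%. The apparent fall is 0.20 × 1.5r / (1.5r + 0.05).

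- 500 nm peak: 1.5 × 0.257 = 0.386; 0.0771/0.436 = about 18%.
- 480 nm peak: 1.5 × 0.106 = 0.159; 0.0318/0.209 = about 15%.
- 440 nm peak: 1.5 × 0.009 = 0.0135; 0.0027/0.0635 = about 4%.

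Without blank subtraction, relative differences therefore shrink towards zero, and more so the further the reading is from the peak. These figures only illustrate the mechanism; none of the assumed inputs is in the protocol.

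**The case against.** The strongest reply is that the deciding fact, the absorption maximum of the WST-1 product, is not in the protocol, and that the word red is a thin basis. This stands as far as size is concerned. It does not remove the direction, which needs only the stated colour and elementary optics.

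Four stronger readings are tempting, and the protocol supports none of them.

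- *The assay keeps only a small fraction of its signal.* A reader might infer this from the table's upper rows. But a red dye peaking at 520 to 540 nm would keep about 34% to 90%. Even at a 480 nm peak with W = 100 nm, a 20% viability fall worth 0.20 × 1.5 = 0.30 AU at the peak leaves 0.106 × 0.30 = 0.032 AU. That is about three times an assumed reader noise of 0.01 AU.
- *The diet comparison is biased.* Absorbance stays proportional to the amount of product wherever the product absorbs, so the protocol's proportionality statement is not contradicted. One wavelength serves every diet period in a within-subject design.
- *Fecal pigment or debris swamps the reading.* Fecal water is the supernatant after ultracentrifugation, and the medium is replaced before the WST-1 solution is added. The text offers no support for a large residual contribution.
- *The primary endpoint of the trial is compromised.* Cytotoxicity is one of six listed primary parameters.

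It is also fair to say that a reader setting can be checked at the bench, and that a short protocol need not describe reference wavelengths or plate normalisation. Their absence is not an error. The point rests on a wavelength that the protocol does fix.

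Finally, the unreduced compound is yellow and so itself absorbs blue light. Simply moving to a shorter wavelength could pick up the substrate. This argues for choosing the wavelength by measurement rather than naming another one from memory.

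**Conclusion.** The point holds in a limited form. The stated wavelength and the stated colour of the product sit poorly together: 570 nm probably reads the product off-peak, which costs sensitivity and precision in one of six primary parameters. This rests on the protocol's description of the product as red and on basic optics.

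The amount lost cannot be determined from the protocol. Systematic distortion of relative differences arises only if the blank is left in the reading, and the protocol does not say whether it is subtracted. This is a cheap improvement to the assay method and does not undermine the trial's design.

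**What to change.** Before any study sample is read, record two absorption spectra: one of WST-1 solution incubated with cells as the protocol describes, and one of a cell-free WST-1 blank. In the assay section, replace 570 nm by the wavelength at which the two spectra differ most; if that is 570 nm, keep it. Using the difference guards against overlap with the yellow substrate. State that the cell-free blank is subtracted from every reading, and use the same setting for all three tests.

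The cost is one extra spectrum beside that of the blank, and a plate-reader setting. No additional samples or volunteers are needed, and nothing changes for the subjects.
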